##### Consent and ethics

After eligibility is confirmed based on data provided by the head of household, the husband of the AGYW is approached to ensure that there are no objections to his wife’s participation in the study; this is done to conform to local cultural norms and to minimize risk. If either the head of household or husband does not assent to participation of both the wife and husband, the couple is determined to be ineligible. A gender-matched RA then accompanies each member of eligible couples to a private location of their choosing to obtain consent and conduct the survey. Verbal consent is assessed after describing the study and participation requirements in detail. In keeping with the World Health Organization guidelines for ethical conduct on research on violence against women [14, 15]. precautions were taken to ensure the safety of adolescent female participants, as well as their privacy, and the confidentiality of their responses. To ensure that married AGYW do not feel pressured or coerced to participate based on husband assent, RAs assure them that consent is truly voluntary and that they are free to decline to participate. Further, only one woman per household is recruited for participation, and questions about experiences of violence were not asked of husbands, in order to minimize any potential risk to her safety arising from her participation. If during the course of the interview, a married AGYW reports IPV, she is offered the option for confidential psychological support to increase her safety. The Pathfinder Program Director, a woman trained in women’s health and safety, is able to provide this service. All study protocols were approved by the Institutional Review Boards (IRBs) at the University of California, San Diego (protocol number 160407S, 03/08/16) and of the Nigerien Ministry of Health. Any modifications to this protocol were reported to the both ethics committees (see Additional file 1).

### RMA intervention

#### Intervention description

The design of the RMA intervention was informed by Pathfinder’s experience implementing similar programs in India [16], Uganda [17], and Burkina Faso [18] that have also included activities involving both men and women, along with community members to promote voluntary contraceptive use.

The two primary components of the RMA intervention include: 1) household visits made by trained community health workers (*relais*), recruited from within the communities to provide education and promote uptake of modern contraceptives and 2) small group discussions held by mentors (also trained community members) to promote dialogue around delaying and spacing births, use of modern contraceptive methods, and relevant cultural and gender norms. The design of the program is based on the socio-ecological model and designed to target the multiple levels of influence on contraceptive use among married AGYW and their husbands in the context of rural Niger. These two main intervention activities are supplemented with community dialogues held in villages across all three districts assigned to any of the three intervention arms to create an enabling environment for healthy timing and spacing of pregnancy (HTSP) and contraceptive method use. Table 1 shows a brief description of all intervention components.

**Table 1 Tab1:** Summary of RMA Intervention Components

	Intervention Component	Intervention Activities and Target Audience	Facilitators and Dosage	District
Primary Intervention Components	Household Visits	Home visits by *relais* are made separately to married adolescent girls and young women (AGYW) and their husbands to provide information and counseling on healthy timing and spacing of pregnancy (HTSP) and contraception.	Female and male *relais*, 12 visits, 1x/month	Loga, Dosso
	Small Group Discussions	Married AGYW – groups foster discussions focused on health and life skills, puberty, contraception, gender, violence; participants also discuss their hopes, dreams, and challenges in a way that promotes social cohesion. Husbands - groups foster reflection and dialogue to encourage more equitable gender norms, support for contraception use for HTSP, positive health seeking behavior for himself and his family, and increased couple communication.	Female and male mentors, 24 sessions for married AGYW 2x/month, 12 sessions for husbands 1x/month	Doutchi, Dosso
Supplementary Intervention Component	Community Dialogues	Community gatekeepers including traditional and community leaders, parents and in-laws participate in community dialogue and reflection sessions to create an environment supportive of HTSP and contraception use.	Four community facilitators (FACOMs) in each district, 1x/month	Loga, Dosso, Doutchi

##### Intervention component 1: household visits

Household visits are conducted by trained *relais* in the homes of married AGYW and their husbands and include provision of education regarding modern contraceptive methods to counter misinformation, promotion of acceptability of contraceptive use and of engagement with the health system to receive family planning (FP) counseling and a modern contraceptive method. *Relais* are gender-matched, i.e., a female *relais* is assigned to each married AGYW, and a male *relais* is assigned to the married AGYW’s husband. Each *relais* speaks to the assigned individual for one hour each month in the home. During these visits, *relais* use project-developed tools and an illustrated guide that supports their delivery of the twelve educational counseling sessions focused on FP counseling. At the first home visit, the *relais* meets with all interested adult family members to explain the RMA program objectives and request permission from the head of household to visit the home and conduct the RMA sessions. Households in this region of rural Niger often comprise multiple related families led by the eldest man.

*Relais* are members of the community who are committed to providing the RMA curriculum in order to help the community. Selection criteria for *relais* include: 1) age 20–45 years, 2) married 3) residing in the village, 4) availability to provide RMA year-round, 5) ability to read and write French (local languages of Hausa and Zarma are not typically written), and 6) favorable attitude towards modern contraception. *Relais* were recruited during village meetings prior to implementation of RMA. In each of the intervention villages assigned to receive household visits, a representative of the program met with the village chief and select community members to present the objectives of RMA, the elements of the intervention, and the selection criteria for *relais*. They then propose names of those that they believe best meet the selection criteria for *relais*.

Training of *relais* takes place over a seven-day period with five days of training sessions, one day for preparation, and one day for reporting. Training is conducted in collaboration with the regional public health division directors as well as health center agents. Training sessions cover modern contraceptive methods, HTSP, gender equity, and adolescent rights with a focus on how to provide education and counseling to participants around these issues.

##### Intervention component 2: small group discussions

Separate small group discussions, conducted by mentors, are held with married AGYW and their husbands. These small groups are formed in each village to foster social cohesion, to build trust, and to promote dialogue related to contraception and SRH within the community. Groups consist of 10 to 13 participants each and are hosted at a health center – twice per month for married AGYW and once per month for their husbands. A female mentor facilitates all group sessions with married AGYW, and a male mentor facilitates all group sessions with their husbands, with additional support for the groups provided by health center staff and community leaders. By collaborating with community leaders, the project hopes to transform resistance to contraception, gender inequitable attitudes, and fertility norms supportive of early and frequent childbearing.

Mentors, who lead the small group discussions, are members of the community and selected by project staff with input from other community members. Selection criteria for mentors were the same as for relais. As with *relais*, training of mentors is conducted in collaboration with the regional directors of public health as well as health center agents. The mentors’ training consists of a five-day workshop with modules on leading and facilitating group discussions about gender equity, the reproductive system, modern contraceptive methods, HTSP, and the health system/services available at each level of the health system.

##### Supplementary intervention component: community dialogues

Community dialogues supplement the two main intervention approaches, household visits and small group discussions, and are a constant in all three intervention arms. Once each month in every intervention village, all adolescent and adult members of the community gather to participate in community dialogue and reflection sessions. This activity is meant to create an environment supportive of modern contraceptive method use and HTSP. Town criers alert community members to these gatherings and village chiefs and religious leaders encourage participation. Sessions are held in the village mosque or center of the village.

Community dialogue facilitators (FACOMs) who lead these sessions - four FACOMs per district (12 in total) - are a mix of men and women selected at the district level by district-level health staff and project staff. Selection of FACOMs also includes input from village leaders. Criteria for selection were the same as for *relais* and mentors. FACOMs receive a seven-day training that, similar to the training of mentors, includes modules on leading and facilitating group discussions related to gender equity, the reproductive system, modern contraceptive methods, and HTSP.

#### Intervention monitoring

To monitor intervention implementation, Nurse Supervisors provided direct supervision of frontline workers (*relais* conducting household visits, mentors leading small group discussions, and FACOMs organizing community dialogues) as well as quarterly focus group discussions. On a monthly basis, Nurse Supervisors visit the frontline workers to ensure the implementation of intervention activities. Intervention implementation is tracked via logs maintained by all frontline workers in which they record the dates and types of intervention activities conducted. At each monthly visit, Nurse Supervisors review logs to identify gaps in implementation. Every other month, frontline workers gather with Nurse Supervisors to plan activities and themes of household visits, small group discussions, and community dialogues. During these meetings, frontline workers and Nurse Supervisors also reflect on what is working well, what is going differently than planned, and what can be improved and how to enact these improvements. At these meetings, frontline workers receive transportation fees and a per diem for their attendance.

In addition, during the first 12 months of intervention implementation, three quarterly meetings were held with a selection of frontline workers (*N* = 12) at the district level. At these meetings, a facilitator held focus group discussions to encourage reflections on challenges to faithful implementation and to collectively develop solutions to address these challenges. Transcripts of these focus groups were used to improve implementation. Focus group discussions were conducted in June 2017, October 2017, and March 2018 with *relais*, mentors and FACOMs.

#### Data collection

As described above, baseline (pre-intervention) data collection occurred from April through June 2016, to be followed by 24-month post-baseline (Time 2) data collection from April – June 2018, and 40-month post-baseline (Time 3) data collection from October – December 2019. Separate questionnaires for wives and husbands were created based on existing reliable and valid measures for low-resource settings such as those included in the Demographic and Health Surveys [19]. Survey measures include items capturing receipt of and participation in each element of the RMA intervention, as well as the primary outcome (modern contraceptive method use), secondary outcomes (knowledge of contraceptive methods, attitudes towards contraception, norms surrounding contraceptive method use, contraceptive method use self-efficacy, intention to use a modern contraceptive method, IPV), and demographics.

Quantitative surveys were first drafted in English, then professionally translated and back-translated to and from French for programming. Research Assistants (RAs), using tablet computers programmed with the survey in French, read all survey instructions and questions verbally to participants in either Hausa or Zarma, based on the preference of the participant. This on-site translation is necessary due to Hausa and Zarma being primarily spoken languages. Research Assistants received extensive training to ensure accurate and reliable translation across RAs. Survey administration takes approximately 45–60 min. Research Assistants were selected, trained and supervised by in-country research partner, L’Initiative OASIS Niger (OASIS), based on RAs previous training and experience in quantitative data collection, as well as their fluency in French and Hausa and/or Zarma. Training of RAs was conducted over five days by OASIS, and included sessions about research ethics and informed consent, procedures to minimize and assess participant distress, referrals for participants reporting IPV, use of the tablet computer to administer the quantitative survey, and data safety, storage and transfer.

Before data collection at 24 months and 40 months, additional steps are taken to ensure participant retention in the study. Staff members from both Pathfinder and OASIS confirm permission from village leaders for upcoming data collection and visit villages to make residents aware that data collection will soon begin. In the process, they confirm participants’ presence in the village and ask residents to encourage participating family/friends who may have migrated for work to return to the village for the data collection period if possible.

#### Primary outcome measure

##### Contraceptive method use

The main outcome of interest for the RMA intervention and evaluation is modern contraceptive method use as reported by the married adolescent wife participants. Current modern contraceptive use will be assessed using data from the following survey items adapted from the DHS [19]: 1) “Are you or your husband currently doing something or using any method to space or delay pregnancy?” 2) if yes, “which method are you currently using?” Thus, if a married AGYW participant responds that, yes, they or their husband are currently using a modern method (IUD, injectable, implant, pill, condom, female condom, emergency contraception, or LAM) they will be considered current modern contraceptive method users. Women pregnant at the time of the survey will be excluded in analyses of this outcome.

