## Background

Recent Demographic and Health Survey (DHS) data from Niger show that 76% of girls marry before the age of 18 and 28% before the age of 15 [1]. Though marrying under age 18 years is permitted by law (legal age of marriage is 15 years for girls) [2], child marriage is associated with poor adolescent health and development, including neonatal and maternal mortality, lack of formal education, and intimate partner violence (IPV). Child marriage is also associated with early childbearing and high adolescent fertility in Niger and multiple other contexts [3–5]. Approximately 9% of girls give birth to a child before age 15 years and 42% give birth between ages 15 and 18 years in this West African nation, [6] with adolescent and total fertility in Niger higher than any country globally [7].

Girls who marry at younger ages in Niger are less likely than those marrying at older ages to utilize maternal health care services (e.g., antenatal visits and institutional delivery), contributing to poor health outcomes [8]. In 2012 in Niger, only 7% of all 15–19 year-old married adolescents (male and female) reported use of a modern contraceptive method [9]. Barriers to modern contraceptive use include lack of access, lack of awareness, misinformation and lack of knowledge, and opposition to use by partners and family [9]. Multiple social norms (i.e., shared social expectations) have been documented in this and other sub-Saharan cultural contexts that additionally impede modern contraceptive uptake [10]. Programs designed to combat early and frequent childbearing in these regions by promoting modern contraceptive use face the challenge of addressing these many barriers.

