### Study overview and design

The purpose of the RMA evaluation study is to assess the efficacy of the RMA intervention using a four-arm cluster randomized control design (October 7, 2017, retrospectively registered, https://clinicaltrials.gov/ct2/show/NCT03226730, Clinical Trials ID: NCT03226730). Specifically, this study seeks to assess whether household visits only (Arm 1), small group discussions only (Arm 2), or a combination of both (Arm 3), as compared to controls (no intervention – Arm 4), improve modern contraceptive method use among married AGYW, age 13–19 years-old, in three districts of the Dosso region of Niger. Based on our conceptual model, we hypothesize that married AGYW that participate in any of the three intervention arms will report: 1) improvement in knowledge of modern contraceptive methods, 2) attitudes more supportive of contraceptive use and gender equity, 3) perceived norms within their communities as more supportive of contraceptive use and gender equity, 4) increased self-efficacy to use a contraceptive method, 5) intention to use a modern contraceptive method, 6) reduction in IPV, and 7) increased use of modern contraceptive methods. Secondarily, reflective of the male engagement elements of RMA, we hypothesize that higher levels of participation of husbands of married AGYW will be associated with greater increases in modern contraceptive use and greater reductions in intimate partner violence, relative to lower levels of husband participation or no participation at all.

Quantitative baseline data (pre-intervention) were collected from April–June 2016 using structured surveys. These same data are collected at 24 months post-baseline (Time 2) from April – June 2018, and 40 months post-baseline (Time 3) from October – December 2019 (see Fig. 1).

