#### Conceptual model

Adapted from Fishbein and Yzer’s modified Theory of Reasoned Action, [12] Fig. 2 depicts the conceptual model of the RMA intervention and the hypothesized pathways through which the intervention promotes change. The primary goal of the RMA intervention is to increase use of modern contraceptive methods among married adolescents age 13–19 years-old and their husbands in Niger. The RMA intervention provides education and counseling on use of modern contraceptive methods and the importance of delaying and spacing pregnancies, particularly for adolescents, alongside promotion of gender equitable attitudes towards, and norms regarding joint decision-making and use of modern contraception. Education on modern contraceptive methods, inclusive of reproductive anatomy and dispelling common misconceptions regarding contraceptives and fertility, is hypothesized to improve knowledge of, attitudes towards, and norms regarding contraceptive use. In parallel, promotion of gender equitable attitudes and norms is hypothesized to reduce perpetration of IPV. Research has demonstrated that IPV is associated with self-efficacy around SRH [13] thus, together, these elements are hypothesized to increase self-efficacy to use modern contraceptive methods. This in turn, will increase intention to use a modern contraceptive method finally resulting in actual modern contraceptive method use. Modern contraceptive methods promoted include intrauterine devices (IUD), injectable contraceptives, contraceptive implants, oral contraceptive pills, male condoms, female condoms, emergency contraception, and lactational amenorrhea (LAM).

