#### Power

Power calculations for our study were conducted a priori based on our primary outcome of interest, modern contraceptive method use (reported by the adolescent wives in our sample). We used pairwise tests for time by treatment effects comparing each intervention group individually to the control group. We chose to account for a moderate intra-cluster correlation coefficient – kappa = 0.05 and an attrition rate of 10%. We also chose to account for the ability to detect an effect size of 2.0 greater odds of contraceptive method use, based on literature reviews of evaluations of interventions seeking to improve contraceptive use, as well as our own experience conducting such trials in other regions. Four arms with 12 clusters nested within each arm, and a sample size of 240 couples per arm (300 couples at baseline with 20% expected attrition; 1200 total baseline participating couples) was calculated to provide 80% power to detect associations of this magnitude.

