##### Intention to use a modern contraceptive method

Intent to use a modern contraceptive method in the next three months will be assessed via a subset of the following four survey questions developed to align with RMA program goals and activities: 1) (for those currently using a modern contraceptive method - IUD, injectable, implant, pill, male condom, female condom, emergency contraception, LAM) “Will you continue to use [Current Method] over the next three months to avoid or delay pregnancy?” 2) (for those not currently using a modern contraceptive method) “Will you use a family planning method in the next three months to avoid or delay pregnancy?” 3) (for those who are currently pregnant) “After your current pregnancy is over, will you use a family planning method to space or delay pregnancy?” and 4) (if ‘yes’ to of any of the above) “Which family planning method would you prefer to use?” If participants respond that they intend to continue use for the next three months, start use in the next three months, or use after current pregnancy, and that the method that they prefer to use is considered a modern (vs. traditional) method, they will be considered as intending to use a modern contraceptive method in the next three months.

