Study analyses will take into account clustering within villages using nested random effects specifications due to repeated measurements over time of individuals nested within villages. Models to assess the role of male engagement will include a three-level predictor of male participation in either household visits or small groups and include only those arms that received that intervention activity. Outcome analyses will use an intent-to-treat approach; per-protocol analyses will be conducted secondarily. Missing data on demographics and birth history will be computed where alternate data is available (e.g. calculating age from date of birth if age is not provided); however, no missing data will be imputed. All scales to be used as outcomes will be assessed for internal reliability at baseline using exploratory factor analysis and Cronbach’s alpha. If scales are multifactorial or not internally reliable, they may be modified to more accurately reflect the intended construct and/or be presented as individual item outcomes. Analyses will be conducted using STATA version 14.2® (StataCorp LLC, 2015) [28] and SAS version 9.4® (SAS Institute Inc., 2018) [29] programming applications. Trial results will be presented to the Ministry of Health of the Republic of Niger then communicated via peer review journals and scholarly meetings as well as meetings with national/international stakeholders.

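### The primary analysis leaves out women pregnant at each survey, a post-randomisation state the programme aims to delay, so it estimates use among non-pregnant women rather than the full intent-to-treat comparison claimed

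*Protocol article*

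**What the plan says.** Under Contraceptive method use, the protocol article defines the primary outcome as the wife's report of current modern method use and adds: "Women pregnant at the time of the survey will be excluded in analyses of this outcome".

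Under Planned analytic approach it says "Outcome analyses will use an intent-to-treat approach; per-protocol analyses will be conducted secondarily", and of missing values, "however, no missing data will be imputed".

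Study overview and design sets the follow-up rounds: "These same data are collected at 24 months post-baseline (Time 2) from April – June 2018", with a further round at 40 months. The Conceptual model lists among the programme's teaching "the importance of delaying and spacing pregnancies, particularly for adolescents". Pregnancy is not among the baseline exclusions under Recruitment and eligibility, and pregnant women are interviewed: the intention outcome has an item "for those who are currently pregnant".

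The Power section plans 240 couples per arm, from "300 couples at baseline with 20% expected attrition; 1200 total baseline participating couples". It mentions attrition but not the loss of pregnant women.

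**The concern.** Pregnancy at 24 or 40 months occurs after assignment, and the behaviour being measured has a strong influence on it. Removing pregnant women removes mostly non-users, and how many are removed from each arm can depend on the intervention. The women left in the two arms are then no longer comparable by virtue of randomisation, although everyone is still analysed in her assigned arm.

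At stake is the meaning of the primary result. A programme that delays pregnancies changes who is in the denominator. A reader given only the result among non-pregnant women could not tell how much of it reflects use and how much reflects who was left to be counted. This concerns a rule the article itself fixes, not a detail that an unseen analysis plan might supply.

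**Working it through.** **The plan's own figure.** 300 × (1 − 0.20) = 240 per arm, so the attrition step reproduces. The stated 80% power cannot be checked, because the control rate, alpha, sidedness and within-woman correlation are not given. The argument does not depend on it.

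**Algebra.** Take one follow-up round and assume no pregnant woman is a current user. In an arm, let u be users and g pregnant women, both as shares of all women, and let k = g/(1 − u) be the pregnant share of non-users. The odds of use after exclusion are

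u/(1 − u − g) = [u/(1 − u)] / (1 − k).

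Hence

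OR after exclusion = OR in all women × (1 − k_control)/(1 − k_intervention).

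The odds ratio is unchanged only when k is equal in the two arms.

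**Illustration (rates assumed; the article gives none for these arms).** Per 100 control women: 12 users, 22 pregnant, 66 non-pregnant non-users, so k_control = 22/88 = 0.25. An odds ratio of 2.0, the effect size in the Power section, gives intervention odds of 2 × 12/88 = 0.2727, or 21.43 users. That is 9.43 extra users and a risk difference of 9.4 points. Control use after exclusion is 12/78 = 15.4%. The result depends on where the extra users come from:

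| Extra users drawn from | Pregnant, intervention | k_intervention | OR after exclusion | Use after exclusion | Risk difference |
|---|---|---|---|---|---|
| Women who would have been pregnant | 12.57 | 12.57/78.57 = 0.16 | 2 × 0.75/0.84 = 1.79 | 21.43/87.43 = 24.5% | 9.1 |
| Half and half | 17.29 | 0.22 | 2 × 0.75/0.78 = 1.92 | 21.43/82.71 = 25.9% | 10.5 |
| Both groups in proportion | 19.64 | 0.25 | 2.00 | 21.43/80.36 = 26.7% | 11.3 |
| Only women who would not have been pregnant | 22.00 | 0.28 | 2 × 0.75/0.72 = 2.08 | 21.43/78 = 27.5% | 12.1 |

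Even where the odds ratio is preserved, the risk difference moves from 9.4 to 11.3 points. That matters because the plan also fits linear models to interpret significant findings.

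**No effect on current use.** Let use be 10% of all women in both arms, with pregnancy at 25% in control and 20% in intervention. The odds ratio in all women is 1.00. After exclusion it is (10/70)/(10/65) = 0.93, an apparent disadvantage produced only by fewer pregnancies. With pregnancy reversed, 20% against 25%, it is (10/65)/(10/70) = 1.08.

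**Sample size.** Excluding 10%, 22% or 30% of 240 leaves 216, 187 or 168 per arm. With 12 villages per arm and an intra-cluster correlation of 0.05, the design effect at 20 women per village is 1 + 19 × 0.05 = 1.95, giving an effective 240/1.95 = 123. At 22% excluded there are 15.6 women per village; the design effect is 1 + 14.6 × 0.05 = 1.73, giving 187/1.73 = 108, a fall of about 12%. In a simple two-sided 5% comparison at one follow-up round (alpha assumed), excluding 10% to 30% lowers power from 71% to 69–63% at a 25% control rate, and from 35% to 34–30% at 7%.

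**The case against.** The best defence is that this is a pre-specified choice of population. Women are still compared by assigned arm. The survey question asks about current action to space or delay pregnancy, which scarcely applies to a woman already pregnant. Pregnant women are not discarded from the study, since they count in the intention outcome. Counting them as non-users has its own flaw: a woman who spaced a birth and then stopped a method in order to conceive would be scored as a non-user. All of this stands. It makes the non-pregnant analysis a legitimate one to report, but it does not make it a comparison of everyone assigned.

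Several stronger readings are tempting and are not supported:

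- A reader might infer that the exclusion flatters the programme. If programme women avoid pregnancy while their control counterparts do not, the odds ratio is attenuated (1.79 in the table). Inflation needs a higher pregnant share of non-users in the intervention arm.
- A reader might infer that pregnancy is simply the result of non-use. Use strongly influences pregnancy but is not its only cause.
- A reader might infer a serious loss of power from 240 falling to 187. Clustering reduces the effective loss to about 12%.
- A reader might take the Background rate of 7% of "married adolescents (male and female) reported use of a modern contraceptive method" as the intended denominator. It covers both sexes, is not a stated design input, and its source cannot be checked here.
- A reader might think the baseline exclusion is equally damaging. Baseline pregnancy is not affected by the intervention. The rule changes who contributes at each round, but a mixed model can use unequal rounds, so that is not in itself a bias.

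**Conclusion.** The point holds in a limited form. As written, the primary analysis conditions on a post-randomisation state the programme aims to change. It estimates use among women not pregnant at the survey, and the article does not reconcile this with its intent-to-treat statement.

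Under the assumed 12% use and 22% pregnancy in controls, an odds ratio of 2.0 could appear as 1.79 to 2.08, and a 9.4-point difference as 9.1 to 12.1 points. These figures rest on rates the documents do not give, on no pregnant woman being a user, and on a plain two-arm comparison rather than the planned difference-in-difference mixed model. They show that the estimate can move in either direction, not by how much it will. The ends of the range are extremes, and an unchanged odds ratio is possible. The missing sample-size allowance is real but secondary.

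**What to change.** Pre-specify an analysis of all surveyed women by assigned arm, with a woman pregnant at a round counted as not currently using at that round, and name it as the intent-to-treat analysis. It should be primary or, at minimum, a named analysis reported beside the present one. Label the present analysis as use among non-pregnant women. Report the number pregnant by arm at every round, so that readers can see whether the two results differ because of use or because of who was excluded. State in the Power section which population the 240 per arm refers to.

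The cost is a sentence or two, one extra model and one table. No new data are needed, because pregnant women are already interviewed. The downside is a lower use rate that is not directly comparable with rates among non-pregnant women, and women who stopped a method in order to conceive will count as non-users.
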